### Population and sample

Women and men 50 years of age and over, residing in the Region of Valencia receiving health care in centers where the ABUCASIS electronic clinical record system has been implanted. Exclusion criteria included: 1) Non-residents in the Region of Valencia, due to limitations for long-term follow-up; 2) Individuals with cognitive impairments that in the opinion of the collaborating clinicians constitutes a hindrance to collecting information about the variables used in the study; 3) People eligible for public healthcare but receiving services through private insurance companies, due to the limitations for collecting data; 4) People who are physically unable to attend their usual primary healthcare center; institutionalization is not a criterion for exclusion as long as the patient can go to the healthcare center; 5) People of Asian or African decent, because of differences in prevalence of osteoporosis due to ethnic origin. The cohort will be recruited opportunistically from among the patients who attend the collaborating primary care centers during a 15-week period.

The sample size has been calculated with the stpower Cox utility of the STATA^® ^statistics package, under the following assumptions: Alpha error (0.05), power (0.80), standard deviation for the densitometry T-score (0.75), square of the multiple correlation among co-variables (0.10), losses to follow-up of 10%, accumulated incidence of hip fracture of 15‰ after five years of follow-up and a capacity to identify as significant hazard ratios of 33% (change in the frequency of an event associated with a unit of change in the co-variable). These calculations results in a sample size of 14,122 individuals over the age of 50 in whom 180 hip fractures are expected to occur at five years of follow-up. The sample will be distributed according to the age and sex structure of the population over the age of 50 in the Region of Valencia and will be assigned in groups of 36 cases among the approximately 400 participating "practices" (two collaborating health care professionals, typically with one doctor and one nurse, per "practice") in order to be able to build a sample that is faithful to the structure of the population of the Region.

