### Statistical analysis

Once the recruiting process has been completed, the cohort baseline data will be analyzed. A description will be made of the patients' characteristics along with their current risk factors. The analysis will be stratified by five-year age-sex subgroups. The appropriate parameters (means, proportions) will be used with each variable with their corresponding 95% confidence intervals (CI95%). A bi-variable analysis will also be made to evaluate the relationships between risk factors that are of most interest. Simple Odds Ratios (OR) will be applied to estimate the strength of association and, when necessary, multiple logistic regression models will be used.

At two and five years of follow-up, an analysis will be made of the strength of association between the risk factors and the incidence of osteoporotic fracture in all locations and in the hip. For this, bi-variable analysis and Cox' proportional hazards models will be used. Additionally, a specific model will be developed to analyze the probability of death once a fracture has occurred (controlling for the effect of the different types of fractures).

Next, the most parsimonious of Cox' proportional hazards models will be applied to two-thirds of the sample (approximately 10,000 subjects randomly selected) to develop a scale to predict the risk of osteoporotic fracture. The scale's prediction capacity will be evaluated with the C statistic, and its calibration will be evaluated with the Hosmer-Lemeshow test, or a similar test. The predictive weights of the risk factors obtained in this model will be applied to the remaining third of the database (approximately 5,000 subjects) to evaluate whether prediction capacity (C statistic > 0.75) and calibration (non-significant Hosmer-Lemeshow test) are maintained. Scaling techniques will then be applied to construct a simplified scale on the basis of the validated model.

Finally, the calibration and the capacity for discrimination of the FRAX scale will be evaluated in the population of the Region of Valencia, Spain. If necessary, the FRAX will be recalibrated to make it more appropriate for the population in question. This time, the weights of the original scale will be used in conjunction with the incidence of osteoporotic fracture derived from our study. If the scale shows poor prediction capacity (statistics < 0,75), or if it is not correctly calibrated, it will be recalibrated with the weights derived from our own scale.

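### One random two-thirds/one-third split keeps a third of the fractures out of the final weights and gives only a small internal validation

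*Protocol article*

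**What the plan says.** The Statistical analysis section sets out three steps.

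- **Association analyses.** "At two and five years of follow-up, an analysis will be made of the strength of association between the risk factors and the incidence". The outcomes are fracture at any site and hip fracture, examined by bivariable methods and Cox models. No split is stated for this step.
- **Development.** Next, "the most parsimonious of Cox' proportional hazards models will be applied to two-thirds of the sample (approximately 10,000 subjects randomly selected"), to give a scale for osteoporotic fracture.
- **Validation.** "The predictive weights of the risk factors obtained in this model will be applied to the remaining third of the database (approximately 5,000 subjects"). Success means a C statistic above 0.75 and a non-significant Hosmer-Lemeshow test.

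A simplified scale is then built from the validated model. If FRAX performs poorly, the study's own weights may be used to recalibrate it.

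Main endpoint names major osteoporotic fracture (hip, clinical vertebral, proximal humerus or wrist). Secondary endpoints lists hip fracture. Population and sample bases the sample size on hip fracture, and Follow-up ties the length of follow-up to the number of hip fractures. Patients are recruited through practices: the sample "will be assigned in groups of 36 cases among the approximately 400 participating" practices.

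**The concern.** Fractures, not subjects, limit what a fracture scale can learn. A single random split spends a third of them on one check and never returns them to the model. The weights are then less precise than the cohort can support, both in the clinical tool and in any FRAX recalibration.

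The check is also weak for its price. A random third of the same cohort differs from the other two-thirds only by chance, so it estimates what a resampling method could estimate from all the data, but with fewer events. The result is judged against a hard cut-off. The Hosmer-Lemeshow criterion also becomes easier to meet as events become fewer, because lack of significance counts as success.

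Finally, the order of the text leaves open whether predictors are chosen from association analyses that include the validation third. If they were, the check would not be fully independent.

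**Working it through.** **Inputs from Population and sample:** "Alpha error (0.05), power (0.80"); "standard deviation for the densitometry T-score (0.75"); "square of the multiple correlation among co-variables (0.10"); "losses to follow-up of 10"%; five-year hip fracture incidence 15 per 1,000; hazard ratio 1.33 per unit. The article states N = 14,122 and 180 expected hip fractures.

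**1. Reproducing the plan's figure** (Cox model, continuous covariate, two-sided test):

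- E = (1.960 + 0.842)² / [0.75² × (ln 1.33)² × (1 − 0.10)] = 190.6 events.
- N = 190.6 / (0.015 × 0.90) = 14,121, which matches the stated 14,122.
- The stated 180 does not follow: 14,122 × 0.015 × 0.90 = 190.6. Both counts are carried below.

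**2. Hip fractures after the split, at five years:**

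| Whole cohort | Development (2/3) | Validation (1/3) |
|---|---|---|
| 191 (implied by the inputs) | 127 | 64 |
| 180 (stated) | 120 | 60 |

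**3. Precision of the weights.** Standard errors scale with 1/√events. Using two-thirds of the events multiplies them by √(3/2) = 1.22, for any endpoint.

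**4. Precision of C in the validation third, hip only** (Hanley-McNeil standard error; 14,122/3 ≈ 4,707 subjects):

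- At C = 0.75 with 64 events: SE 0.036, 95% CI 0.68 to 0.82. With 60 events: SE 0.037, again 0.68 to 0.82.
- At C = 0.75 with all 191 events in 14,122 subjects: SE 0.021, 95% CI 0.71 to 0.79. This is sampling error only.
- Observed/expected ratio, limits exp(±1.96/√events): 0.78 to 1.28 with 64 events, 0.87 to 1.15 with 191.
- Hosmer-Lemeshow by deciles: 64/10, about 6 events per group.

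**5. The 0.75 cut-off, hip only, 64 events:**

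- True C 0.78 (SE 0.034): probability of passing = Φ(0.03/0.034), about 81%.
- True C 0.73 (SE 0.036): probability of passing = Φ(−0.02/0.036), about 29%.

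**6. Main endpoint.** The article gives no rate for major osteoporotic fracture; Follow-up says only that fractures at other sites are much more frequent. Taking 2 to 4 times the hip count, as an assumption:

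| Multiple | Validation events | Half-width of 95% CI at C = 0.75 | O/E limits |
|---|---|---|---|
| 2 | 128 | 0.049 | 0.84 to 1.19 |
| 3 | 192 | 0.040 | 0.87 to 1.15 |
| 4 | 256 | 0.035 | 0.88 to 1.13 |

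**The case against.** A held-out random third is a recognised, if inefficient, form of internal validation, and nothing in the article contradicts it. Four stronger readings are tempting, and the article does not support them.

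- **That about 64 events is the count for the scale.** The split is described for an osteoporotic-fracture scale, and hip fracture is secondary. The hip figures apply only to a hip-specific scale. That case still matters, because Follow-up speaks of scales and links them to having enough hip fractures. They are also five-year figures; Design allows extension to ten years depending on hip fracture incidence, which would add events to both parts.
- **That planned power falls from 80% to about 63%.** The sample size calculation powers a hazard-ratio test, which belongs to the association analysis, and no split is stated there. Power to reject a null coefficient is also not a measure of how well a scale predicts.
- **That predictor choice has already used the validation third.** This rests on the order of the paragraphs. The text equally allows selection inside the development part, and the candidate variables came from literature and guidelines. It is an ambiguity, not demonstrated leakage.
- **That the split fails as a test of transportability.** The scale is claimed only for the Region of Valencia, so this is a secondary matter.

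What remains is the loss of efficiency, which applies to every endpoint, and the imprecise check, which is clear for hip fracture and milder for the main endpoint.

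**Conclusion.** The point holds as one about efficiency and precision. As described, the final weights rest on two-thirds of the events, with standard errors about 22% wider than necessary. That figure needs only that information is proportional to events.

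The validation third is internal and smaller than it need be. For hip fracture at five years it holds 60 to 64 events (from the stated 180 or the implied 191), C is known to about ±0.07, and passing or failing at 0.75 is partly chance. For major osteoporotic fracture the size cannot be fixed from the article; under the assumed 2 to 4 times the hip count, C is known to about ±0.05 to ±0.035. Whether predictors are selected on the validation third is left open and should be stated. The change is worth making, because developing and validating the scale is the study's main objective.

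**What to change.** - Develop the scale on the whole cohort.
- Validate internally by bootstrap, repeating variable selection and construction of the simplified points scale in every resample. This also settles where selection takes place, and brings the simplified scale, which the text builds only after the validation step, into the check.
- Report optimism-corrected C and calibration slope with confidence intervals, for major osteoporotic fracture and for hip fracture.
- Optionally, add internal-external cross-validation that leaves out groups of Health Departments in turn, to show heterogeneity within the Region. Single Departments are too small: 191/23 is about 8 hip fractures each.

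Cost: a slightly longer validation paragraph, analysis code and more computing. No new data and no change to recruitment are needed. The optimism correction adds some uncertainty of its own, so the gain in precision of C will be somewhat less than the comparison of ±0.07 with ±0.04 suggests.

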## Background

Osteoporosis is a systemic disease of the skeleton, characterized by the deterioration of the bones' macro and microstructures that leads to a loss in bone mass and the reduction in the bones' resistance increasing propensity to bone fracture [1]. At present, osteoporosis is highly prevalent, with an incidence that is rising due to the greater life expectancy of today's societies. Osteoporosis is a silent disease, yet has a major clinical impact because of its association with an increased risk of fracture. The most relevant events associated with osteoporosis are osteoporotic fractures and their consequences. Most frequently, events occur in the dorsolumbar spine, the hip and the wrist.

Hip fracture is the most serious consequence of osteoporosis. In Spain it is estimated an incidence of hip fracture in people over 50 years-old between 2-3 cases per 1,000 inhabitants/year [2-5], with a male/female distribution of 2-3:5. These figures increase considerably with age, and in subjects over the age of 60, the incidence of hip fracture is 5-7 cases per 1,000 inhabitants/year, with greater occurrence among women [6,7]. Regarding vertebral fractures, prevalence and incidence rates vary considerably, depending on the population and the criteria used to define a fracture. In subjects over the age of 50 in the Region of Asturias, Spain, prevalence was 27.2% in women and 20.8% in men [8]. In a population-based study recently conducted by our group in post-menopausal women in the city of Valencia, the prevalence of morphometric vertebral fracture was 21% in women over 50, and 46% in women over 75 [9].

According to data recently published in the Region of Valencia, Spain [10] the annual number of hospital admissions for fractures of the hip, vertebrae and forearm (fractures that are not due to major traumatism assessed using the Hospital Discharge Data Set) has increased in absolute values in the population over the age of 64. Discharges in the Region for hip fracture have gone from 3,329 in 2000 to 4,510 in 2006. Distal fractures of the forearm went from 341 to 496 during the same period. The number of vertebral fractures -that usually are managed without hospitalization- remained stable. Osteoporotic fracture has major social and health impact. Mortality for hip fracture in hospitalized patients is between 5 and 8%, and jumps to 20-30% during the first year [11]; only one third of survivors recover their pre-fracture condition.

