Today, while there are effective drugs that reduce the risk of osteoporotic fracture, yet there is no broadly accepted criteria that can be used to estimate risks and decide who should receive treatment. One of the actual priorities of clinical research is to develop a set of simple and readily-available clinical data that can be used in routine clinical practice to identify patients at high risk of bone fracture, and to establish thresholds for therapeutic interventions. Such a tool would have high impact on healthcare policies. Because hip fracture is associated with the greatest disease burden, efforts are being concentrated in this area.

Studies have shown that the loss of bone mineral density (BMD), as measured by dual energy x-ray absorptiometry (DXA) is a good predictor of fracture, particularly in older women. The risk of osteoporotic fracture nearly doubles for each standard deviation decrease in BMD [12,13]. Nevertheless, there are many other factors that contribute to osteoporotic fracture, and the loss of BMD only identifies part of the risk. Studies have shown that normal BMD does not mean that there is no risk of osteoporotic fracture. Some of the Clinical Risk Factors (CRFs) involved in osteoporotic fracture only affect bone mass, and may be used to identify thresholds for testing with BMD. Other CRFs are associated with increased risk of osteoporotic fracture independently of BMD [14,15], and looking at these will improve the prediction of risk fracture [16,17]. For these reasons, different proposals have been forwarded to estimate the risk of osteoporotic fracture taking into account the different CRFs (as occurs when estimating the risk of cardiovascular events), with or without information on BMD.

This tools aims to predict the risk of an incident osteoporotic fracture during a specific period of time, usually ten years. Black et al [18], with their Fracture Index, were among the first to propose a set of criteria to predict vertebral, non-vertebral and hip fractures. More recently, Robins et al. [19], and Vazquez et al., in Spain [20], have proposed other scores although today FRAX is the scale most widely accepted internationally [21].

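### Validating the scale by C > 0.75, with no age-and-sex reference model, cannot show that the clinical risk factors add to prediction

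*Protocol article*

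**What the plan says.** All references are to the Protocol article.

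- **Statistical analysis, development.** "the most parsimonious of Cox' proportional hazards models will be applied to two-thirds of the sample", chosen at random, to build the scale.
- **Statistical analysis, validation.** The weights go to the remaining third (about 5,000 people) "to evaluate whether prediction capacity (C statistic > 0.75) and calibration (non-significant Hosmer-Lemeshow test) are maintained". The simplified scale is then built from the validated model.
- **Statistical analysis, FRAX.** The same cut-off is used: "If the scale shows poor prediction capacity (statistics < 0,75), or if it is not correctly calibrated", FRAX is recalibrated with the study's own weights.
- **Other variables.** Age and gender are listed with the clinical factors as independent variables.
- **Population and sample.** Entry is from age 50 with no upper limit. "The sample will be distributed according to the age and sex structure of the population over the age of 50".
- **Background.** The case for looking beyond bone density is that "Other CRFs are associated with increased risk of osteoporotic fracture independently of BMD [14,15], and looking at these will improve the prediction of risk fracture".
- **Main endpoint and Secondary endpoints.** The main endpoint is a four-site composite (hip, clinical vertebral, proximal humerus, wrist). Hip fracture alone is secondary.

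No age-sex model, increment in C or within-age C is named beside the 0.75 bar.

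**The concern.** A C statistic pooled over everyone aged 50 and above asks how often a person who fractures was ranked above one who does not. Where fracture risk climbs with age, most such pairs differ in age, and ranking by age does much of the work. The rule compares the resulting C with a constant, not with what age and sex would have achieved in the same people.

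This is not a matter of sampling error, and a larger validation sample would not cure it. A scale whose clinical factors add nothing can pass where the age gradient is steep. A scale whose clinical factors add real information can fail where it is shallow.

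At stake is what a pass may be taken to mean. The scale is intended for routine visits and to support treatment thresholds. Readers would naturally take a validated scale as evidence that recording the clinical factors is worthwhile, and this criterion does not supply that evidence.

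**Working it through.** **1. The plan's own figure.** The plan states no expected C, so the nearest figure to reproduce is the sample size. With two-sided alpha 0.05, power 0.80, SD 0.75, hazard ratio 1.33, R² 0.10, cumulative hip incidence 15 per 1,000 and 10% losses:

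- Events = (1.960 + 0.842)² / [0.75² × (ln 1.33)² × (1 − 0.10)] = 190.6
- N = 190.6 / 0.015 / 0.90 = 14,121, against the stated 14,122. It reproduces.

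**2. Size of the validation third.** 14,122/3 = 4,707 and 14,500/3 = 4,833; 4,800 is used below. Hip fractures in it: 180/3 = 60 from the stated total, or 4,800 × 0.015 = 72 before losses. That is about 60 to 70.

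**3. C for age and sex alone.** Five-year risk at age *a* is p = 1 − exp(−k · g^((a−50)/10) · r^female), where g is the hazard ratio per decade, r is the female:male ratio and k is set to give the overall risk. Then

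C = Σᵢⱼ wᵢpᵢ wⱼ(1−pⱼ)[1(ηᵢ>ηⱼ) + ½·1(ηᵢ=ηⱼ)] / [Σwᵢpᵢ · Σwⱼ(1−pⱼ)],

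with w the age-sex shares and η the log hazard.

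- From the documents: hip risk of 15 per 1,000 over five years; r between 5/3 = 1.67 and 5/2 = 2.5 (Background); 2.0 is used.
- Assumed: 54% women, several plausible age distributions over 50, and the age gradient g.

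C reaches 0.75 when the hazard rises about 2.0 to 2.3-fold per decade. Doubling every 8 years is 2^(10/8) = 2.38 per decade, just above that.

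**4. Hip fracture.** Ranges cover separate runs with different assumed age mixes. The last column is the share of simulated validation samples of 4,800 in which the age-sex score alone exceeds 0.75.

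| Rate doubles every | Age-sex C | Share with C > 0.75 |
|---|---|---|
| 5 years | 0.85–0.88 | 100% |
| 6 years | 0.82–0.84 | 99–100% |
| 7 years | 0.79–0.81 | 88–94% |
| 8 years | 0.76–0.78 | 61–81% |
| 10 years | 0.72–0.74 | 17–26% |

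In one run a ten-group calibration test was added, using the true age-sex risks. Both halves of the rule were passed in 94%, 92%, 89%, 71% and 22% of samples, in the order of the table. The calibration requirement gives little protection, because an age-sex model checked in a random third of its own cohort is usually calibrated.

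**5. Four-site main endpoint.** The documents give neither an age gradient nor an incidence for it. Assumed: gradients per decade of 2.5–4 for hip, 2.0 for vertebral and 1.1–1.8 for wrist and humerus; hip 30–45% and vertebral 20–25% of events; overall risk 4.5%. The age-sex C is then 0.68 to 0.79. With a single gradient and an assumed 5% risk, C > 0.75 occurs in 15%, 86% and 99.5% of samples at 2.0, 2.3 and 2.5 per decade. In another run it occurs in about 0–1% when the rate doubles every 12 years or more slowly.

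**6. Do the Background's hip rates fix the gradient?** They are "incidence of hip fracture in people over 50 years-old between 2-3 cases per 1,000 inhabitants/year" and "in subjects over the age of 60, the incidence of hip fracture is 5-7 cases per 1,000 inhabitants/year, with greater occurrence among women". The smallest ratio of the over-60 to the over-50 rate is 5/3 = 1.67. The largest possible ratio, with no fractures at all at ages 50–59, is 1 divided by the over-60 share: 1/0.71 = 1.40 to 1/0.60 = 1.67 for assumed shares of 71% to 60%. The two rates carry different citations and cannot be fitted together by any realistic gradient. They are not used as an anchor.

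**The case against.** - **The objective is a scale for this population, not proof that it beats age and sex.** This is fair. The sentence on risk factors improving prediction is framed against bone density, and the Background counts age among the risk factors of an earlier score. So the rule does not contradict a stated hypothesis. It remains that a pass cannot support a statement about the clinical factors.
- **Contribution is examined elsewhere.** Objective 2 estimates each factor's association, including within five-year age-sex subgroups, and the scale comes from the most parsimonious model. Idle factors should largely drop out. This weakens any suggestion that a long list of useless factors would go unnoticed. But an association in the development data is not a measure of predictive gain in the validation third.
- **The rule has two halves, and FRAX is a comparator.** Both are true. Neither isolates the clinical factors: calibration is usually met by an age-sex model (step 4), and FRAX itself contains age and sex and is judged by the same 0.75.
- **The article is condensed and no SAP is shown.** The absence of a reference model would not by itself be a finding. The point is that the article does fix a numerical criterion, and that criterion is uninformative on this question.
- **Stronger reading.** A reader might infer that age and sex would almost always carry the scale past the bar, citing the ratio of 1.67. Step 6 shows that the ratio cannot bear this, and step 5 shows that it is unsupported for the main endpoint.

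**Conclusion.** The point holds in a limited form. The discrimination criterion is absolute and has no age-sex reference, so meeting it, even with the calibration test, does not show that the clinical risk factors add anything.

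- **Hip fracture:** age and sex alone plausibly meet the bar, with C about 0.76 to 0.88 if the rate doubles every 8 years of age or faster. That gradient is an assumption. The documents say only that hip fracture rises considerably with age.
- **Four-site main endpoint:** undetermined from the documents, with an age-sex C of roughly 0.68 to 0.79 under assumed site gradients and shares.

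The documents do not support saying that the rule would nearly always declare success, or that the scale will turn out to be age and sex in disguise. The same bar also triggers the re-weighting of FRAX, so that decision too depends partly on the cohort's age mix.

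**What to change.** In Statistical analysis, add an age-and-sex-only Cox model fitted in the same development two-thirds and applied to the same validation third. For each fracture endpoint for which a scale is claimed, report:

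- the C of the age-sex model, the C of the scale, and their paired difference with a 95% bootstrap interval;
- the scale's C within age bands.

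Keep C > 0.75 and calibration as minimum requirements. State that any claim that the clinical factors improve prediction rests on the difference from the age-sex model.

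Making a positive lower confidence limit for the difference the sole success rule would go too far. With about 60 to 70 validation hip fractures, simulated real gains in C (about 0.007 to 0.026, from extra factors with an assumed log-hazard SD of 0.4 to 0.6) met that rule in only about 25% to 65% of samples. The absolute floor would also be lost.

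The cost is one extra model, a bootstrap on data already collected and a change of wording. The downside is that the increment may be small, and imprecise for hip fracture, so the headline claim may become less favourable.

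### A non-significant Hosmer-Lemeshow test and a C point estimate above 0.75 are too weak a validation rule: moderate miscalibration often passes, and usually does if the rule is applied to hip fracture

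*Protocol article*

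**What the plan says.** The Statistical analysis section of the protocol article fits the most parsimonious Cox model in a random two thirds of the sample, to build a scale for osteoporotic fracture. Of that scale it says "its calibration will be evaluated with the Hosmer-Lemeshow test, or a similar test". The weights are then carried to the remaining third, put at roughly 5,000 subjects, "to evaluate whether prediction capacity (C statistic > 0.75) and calibration (non-significant Hosmer-Lemeshow test) are maintained". The simplified scale for clinical use is built on the model so validated. The same 0.75 cut-off, again without an interval, helps decide whether FRAX keeps its original weights.

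The Abstract (Discussion) and the end of the Background say that the scale will help to identify intervention thresholds. Population and sample sizes the study on hip fracture, with an "accumulated incidence of hip fracture of 15‰ after five years of follow-up" and 180 expected hip fractures.

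**The concern.** The calibration criterion runs the wrong way. A goodness-of-fit test that does not reject may mean that predictions are accurate or that there were too few fractures to show that they are not. The smaller the validation set, the easier the pass. The p-value also does not say whether risks are too high or too low, or by how much.

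A treatment threshold is a cut on absolute risk. A scale that is 25% out moves people across it while ranking them exactly as before, so C gives no protection against that error. C has its own difficulty: a point estimate is compared with 0.75 although the hip event count leaves it imprecise.

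At stake is whether a scale reported as validated has been shown to give the right risks.

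**Working it through.** **Events available.** The inputs in Population and sample are alpha 0.05, power 0.80, "standard deviation for the densitometry T-score (0.75"), "square of the multiple correlation among co-variables (0.10"), 10% losses, hip incidence 1.5% and a hazard ratio of 1.33. Two-sided:

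- E = (1.960 + 0.842)² / [0.75² × (ln 1.33)² × (1 − 0.10)] = 190.6 events
- N = 190.6 / 0.015 / 0.90 = 14,121.3, so 14,122, as stated.

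The text gives 180 events where its inputs give 190.6. The validation third holds 14,122/3 = 4,707 people and 180/3 = 60 to 190.6/3 = 63.5 hip fractures. The discrepancy does not affect what follows.

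**How often the test passes a miscalibrated hip scale.** Simulation of 4,707 people with about 60 hip fractures, a normally distributed linear predictor, a binary five-year outcome, ten risk groups, 5% level and actual C 0.78. Percentage non-significant:

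| Miscalibration | 10 df | 8 df |
|---|---|---|
| O/E 1.2 | 79 | 67 |
| O/E 1.3 | 62 | 50 |
| O/E 1.5 | 33 | 23 |
| O/E 2.0 | 3 | 2 |
| O/E 0.83 | 95 | 88 |
| O/E 0.77 | 91 | 82 |
| O/E 0.67 | 64 | 41 |
| O/E 0.5 | 0 | 0 |
| Slope 0.9 | 85 | 76 |
| Slope 0.8 | 62 | 49 |
| Slope 0.7 | 26 | 18 |
| Slope 0.6 | 3 | 2 |

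With about 64 events, and 0.78 taken as the C that the predictions imply, the 10 df pass rates are 67% at O/E 1.25, 93% at O/E 0.75, 73% at slope 0.8 and 15% at O/E 1.5. Ten df suits weights carried to new data; 8 df is the usual software default.

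**Both criteria together** (60 events, actual C 0.78, 10 df): 71% pass at O/E 1.2, 56% at O/E 1.3, 79% at O/E 0.77 and 61% at slope 0.8.

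**Major fracture.** The documents give no five-year incidence, so it is assumed.

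- At 3-5%, a 25% error passes about 15-62% of the time and slope 0.8 passes 48-57%.
- With the observed incidence set at 3%, 4.5% and 6% and actual C 0.75, O/E 1.25 passes 50%, 32% and 19%, and slope 0.8 passes 54%, 40% and 34%. At 6% and O/E 0.77 the pass rate is 7%.

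**C rule for hip.** With about 60 events the SD of C is about 0.03. A true C of 0.70 passes 6% of the time, 0.72 passes 18%, 0.75 passes 50% and 0.78 passes about 85%. The Hanley-McNeil standard errors for 64 events (0.0365 at 0.72, 0.0344 at 0.78) give 21% passing and 19% failing.

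**Precision of the alternative.** For perfect calibration with 60 events, the 95% interval of O/E is exp(±1.96/√60) = 0.78 to 1.29. A lower limit of C above 0.75 needs an observed C near 0.75 + 1.96 × 0.03 = 0.81.

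The simulations ignore censoring within five years.

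**The case against.** - **The outcome.** The paragraph names a scale for osteoporotic fracture, objective 5 promises only that, and hip fracture is a secondary endpoint. A reader might infer that the protocol sets up a hip scale to be validated by this rule; no section says so. The inference rests on the Abstract (hip and/or major fracture as outcome), the hip-based sample size, and Follow-up, where the scales (plural) wait for enough hip fractures. It is reasonable, but it is an inference. This stands.
- **Overall shifts are unlikely.** Validation uses a random third of the same cohort. Development has about 190.6 × 2/3 = 127 hip events, so the SE of log risk is 1/√127 = 0.089. A true O/E above 1.25 then has probability about 0.6% (ln 1.25/0.089 = 2.5), and one below 0.75 about 0.06%. This stands: overfitting, seen as a slope below 1, is the realistic failure, and slope 0.8 is the row that matters most.
- **C may catch overfitting.** If overfitting also pulls the actual C to 0.72-0.74, the C rule passes only 18-41%. The 61% joint pass rate at slope 0.8 assumes that C stays at 0.78. This limits the joint figure, not the criticism of the calibration test.
- **Any cut-off is a coin toss at the cut-off.** True. It would overstate the case to say that the C rule rewards chance, since a true C of 0.70 passes only about 6% of the time. What remains is the missing interval.
- **Detail left to the analysis plan.** Allowing a similar test leaves room for a version suited to censored data, so the article cannot be read as ignoring censoring. But the pass rule itself is stated, and any similar test judged by non-significance has the same fault.

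**Conclusion.** The point holds in moderate form. Non-significance is stated as the calibration criterion and cannot bear that weight. For hip, if the rule is used there, errors of about 25% in absolute risk pass roughly two times in three (under-prediction) to nine in ten (over-prediction), and slope 0.8 passes 60-75% of the time, all with 10 df; 8 df gives lower rates. For major fracture the test has more power, and whether it passes more often than not depends on the assumed incidence.

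A reader might infer that the rule usually passes a badly wrong scale. The figures do not support that: under-prediction at O/E 1.5 passes only 15-33% of the time, and O/E 2.0, O/E 0.5 or slope 0.6 almost never. Large over-prediction is caught less well, with O/E 0.67 passing 64% (10 df) or 41% (8 df).

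The results rest on 60-64 hip events in the validation third, an actual or predicted C of 0.78 for the hip pass rates, ten risk groups, and an assumed incidence for major fracture. The logical fault depends on none of these.

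**What to change.** In Statistical analysis, remove the non-significant Hosmer-Lemeshow result as a condition for validation. Judge calibration by the five-year O/E ratio, the calibration slope and a calibration plot, with observed risk estimated allowing for censoring and death. Report these and C with 95% confidence intervals, and read the 0.75 benchmark with its interval, for FRAX as well.

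Do not impose a fixed band such as 0.8-1.25 on the O/E interval for hip. With 60 events even perfect calibration gives about 0.78 to 1.29, so no hip scale could meet it. Either set any band to the expected number of events, or report hip calibration as an estimate with its interval and make no pass/fail claim. Resampling validation on all 180 events is an option; the corresponding O/E precision is exp(±1.96/√180) = 0.86 to 1.16.

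The cost is protocol wording and standard software, with no new data. The drawback is that calibration and validation become harder to claim, above all for hip.
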